Figure 1. Arm 1 delivers standard ANC/PNC care only and is the pure control. Arm 2 delivers standard ANC and PNC care, with the addition of early pregnancy testing in the community and obstetric ultrasound performed by primary ANC providers. Arm 3 delivers group ANC/PNC, and Arm 4 delivers group ANC/PNC with the addition of early pregnancy testing and ultrasound. In health centers randomized to group care (Arms 3 and 4), this model will follow the opt-out standard of care for facility-based ANC and PNC. This design makes it possible to analyze differences between group care and standard care and also to assess if those effects are mediated by early pregnancy testing in the community or the availability of ultrasound (especially for early GA assessment) at the health center.

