**Figure 1. f1:**
[figure not shown]
Facility-level randomization of 36 health centers included in a cluster randomized controlled trial of group antenatal care and postnatal care in Rwanda. Arm 1 delivers standard antenatal and postnatal care only and is the pure control. Arm 2 delivers standard antenatal and postnatal care, with the addition of early pregnancy testing in the community and obstetric ultrasound performed by primary antenatal care providers. Arm 3 delivers group antenatal and postnatal care, and Arm 4 delivers group antenatal and postnatal care with the addition of early pregnancy testing and ultrasound. In health centers randomized to group care (Arms 3 and 4), this model will follow the opt-out standard of care for facility-based antenatal and postnatal care. This design makes it possible to analyze differences between group care and standard care and also to assess if those effects are mediated by early pregnancy testing in the community or the availability of ultrasound (especially for early gestational age assessment) at the health center. HC, health center; US, ultrasound; PT, pregnancy testing.

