### Sample size

Based on a review of RCT results included in the 2015 Cochrane Review of group versus conventional antenatal care for women
^24^, we assume the intraclass correlation coefficient (ICC) between Arms 1 and 2 and Arms 3 and 4 will be no larger than 0.01. We assume the standard deviation of GA at delivery is no larger than 4.3 weeks under both intervention and control arms. At 5% significance, with 36 facilities, this trial is powered (80%) to detect a 0.5-week difference in GA at delivery with 214 observations (ANC and outcome) per facility. Assuming a follow-up rate of 70%, 306 women per facility will be required. Just over 11,000 women will be recruited and we expect to follow almost 8,000 mother-newborn dyads through the period of the six-week PNC visit. At an average rate of 23 eligible recruits per month per facility, the total study duration will be (a) 14 recruitment months (from the end of May 2017 to August 2018, (b) an additional six to seven months to observe the outcomes of the last cohort of women recruited (February 2019), and (c) three additional months to complete data processing and analysis (May 2019).

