### Statistical analyses

To compare the study groups, socio-demographic and reproductive health characteristics, and health care facility descriptive bivariate analyses stratified by study arm will be conducted using Chi-square and Student’s t-test statistics for categorical and continuous data, respectively. Similar unadjusted bivariate analyses will be presented for the primary and secondary outcomes. Unadjusted, intention-to-treat generalized estimating equations (GEE) linear regression with robust variance estimation analyses will be conducted to assess the effectiveness of the treatment regimen on the primary outcome variable, gestation at delivery, and analogous linear and logistic analyses of will be conducted to assess continuous and categorical secondary outcomes (Model 1). For these outcomes, similar analyses will be conducted to control for design effect (Model 2) and the effects of any additional unforeseen differences in measured study group characteristics (Model 3). Model 3 will include all covariates that are statistically significant and judged as important differences between the study group (e.g. not simply significantly different due to large sample size) as identified by a backward stepwise Wald analysis (Model 3), which removes the covariate least associated with the outcome, and continues in that manner to remove covariates not significantly associated with the outcome at the α=0.05 level.

Model 1: Outcome=Independent Causal VariableModel 2: Outcome=Independent Causal Variable, adjusted for design effectModel 3: Outcome=Independent Causal Variable, adjusted for design effect plus (retained) covariates

Additionally, we propose comparing these methods with data-adaptive targeted maximum likelihood estimators (TMLE)
^25^. These would attempt to leverage the hierarchical structure of the data and would adjust for covariates through a data-adaptive algorithm. Multi-level analyses to adjust for facility-level characteristics will be considered.

The main analyses will compare the control group (Arms 1+2) with the intervention group (Arms 3+4). Subanalyses by study arm will be conducted.

Arm 1: Standard ANC/PNC careArm 2: Standard ANC/PNC care, with early pregnancy testing and ultrasoundArm 3: Group ANC/PNC onlyArm 4: Group ANC/PNC care, with early pregnancy testing and ultrasound

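### The design cannot show mediation by pregnancy testing or ultrasound, only modification of the group-care effect by the combined package, and no named analysis estimates that modification

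*Protocol article*

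**What the plan says.** The protocol article's Study design section randomises group care within each matched pair. It then matches pairs into quadruples and randomises one pair in each quadruple to add ultrasound at the health center together with community pregnancy tests. From this it claims that the design makes it possible "also to assess if those effects are mediated by early pregnancy testing in the community or the availability of ultrasound". The Figure 1 legend repeats the claim: "assess if those effects are mediated by early pregnancy testing in the community".

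The Statistical analyses section sets the main comparison as Arms 1+2 against Arms 3+4 and adds: "Subanalyses by study arm will be conducted". Models 1 to 3 each show a single exposure term, with adjustment for the design and then for covariates. No product term or difference between effects appears.

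The Sample size section covers only the pooled comparison: "At 5% significance, with 36 facilities, this trial is powered (80%) to detect a 0.5-week difference in GA at delivery".

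**The concern.** A mediator must be something the treatment can change. Here the package is fixed by a separate randomisation, so delivering group care cannot alter whether a facility has it. The claim also joins the two components with an *or*, although every facility receives both or neither, so their roles cannot be separated.

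The layout does support a question about effect modification: is the group-care effect with the package (Arm 4 minus Arm 2) different from the effect without it (Arm 3 minus Arm 1)? Nothing in the Statistical analyses section makes that comparison.

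Two misreadings could follow. If readers or analysts look at significance separately in the two halves of the trial, they may report that the effect depends on the package when it does not. Conversely, a non-significant comparison of the effects may be taken to show no dependence, although the test has little power.

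**Working it through.** **Inputs.** All come from the Sample size section unless noted.
- SD of gestational age 4.3 weeks, given as an upper bound: "We assume the standard deviation of GA at delivery is no larger than 4.3 weeks under both intervention and control arms".
- ICC 0.01, also an upper bound: "will be no larger than 0.01".
- Effect 0.5 week; 214 analysable women per facility; 36 facilities; 5% significance, taken as two-sided because sidedness is not stated.
- Nine facilities per arm, derived from the Study design section: 36 / 4 = 9.

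**Step 1: reproduce the plan.** Variance of a facility mean: v = 4.3² × (0.01 + 0.99/214) = 0.270. Main-effect SE = √(4v/36) = 0.173 week. A noncentral t with 34 df gives 80.0% power for 0.5 week, and 214 is the smallest number per facility that reaches 80%. The recruitment figure also follows: 214 / 0.70 = 305.7, rounded up to 306.

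**Step 2: one package stratum (9 versus 9 facilities).** SE = √(4v/18) = 0.245 week. Power for a true 0.5 week is 48.3% with 16 df (53% by the normal approximation; 43.5% with 8 df, as for pair differences at the same SE).

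**Step 3: compare significance across strata when the effects are equal.** The contrasts Arm 3 − Arm 1 and Arm 4 − Arm 2 share no facilities. With power p in each, the chance that exactly one is significant is 2p(1 − p).
- At p = 0.483: 2 × 0.483 × 0.517 = 49.9% (49.8% normal, 49.1% with 8 df).
- Since 2p(1 − p) cannot exceed 50%, this is the ceiling.

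Sensitivity of that probability (normal approximation):

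| Scenario (equal true effects) | Exactly one significant |
|---|---|
| 0 week, ICC 0.01 | 9.5% |
| 0.25 week, ICC 0.01 | 29% |
| 0.5 week, ICC 0.01 | 49.8% |
| 0.75 week, ICC 0.01 | 23% |
| 1.0 week, ICC 0.01 | 3% |
| 0.5 week, ICC 0.005 | 41% |
| 0.5 week, ICC 0.002 | 25% |
| 0.5 week, ICC 0.01, Arms 3 and 4 each against Arm 1 | about 33% |

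**Step 4: test the difference in effects directly.** SE of (Arm 4 − Arm 2) − (Arm 3 − Arm 1) = √2 × 0.245 = 0.347 week. When the effects are equal, the test rejects 5% of the time (4.98% in simulation).
- Power for a 0.5-week difference in effects: 28.8% with 32 df (30% normal; 27.3% with 16 df for pair differences).
- Power for a 1.0-week difference: 79.9% with 32 df (77.3% with 16 df). By the normal approximation, 80% is reached at 0.97 week.

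The SEs for main effect, stratum and interaction stand in the ratio 1 : √2 : 2. That ratio holds for any outcome with equal facility-level variance across arms. Gestational age is used here because it is the only outcome for which the protocol gives planning figures.

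**The case against.** The strongest objection is that the protocol never says what its by-arm subanalyses test. It gives no contrast, null hypothesis or decision rule and does not tie them to the mediation claim. A reader might infer that each arm contrast will be tested against zero and the results compared. The text does not support that inference: a four-level arm model could contain the interaction contrast, and an analysis plan that is not shown may specify it. This stands, and the point must not accuse the trial of planning to compare p-values.

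A reader might also infer that equal effects would look different about half the time in general. The table shows otherwise. The figure is a ceiling, reached near the plan's own inputs, and those use upper bounds for SD and ICC and ignore any gain from matching. This stands too.

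It can further be said that effect modification is not among the listed aims, that by-arm work is already ranked below the main analysis, and that no power is claimed for it. That limits the weight of the point but does not remove it: the article states twice that the design can answer this question.

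Finally, reducing all arm-level results to description would conflict with Table 2, which plans secondary outcomes for comparison across arms, and with the secondary aim on ultrasound and pregnancy testing. That is correct, and those comparisons should stay.

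None of this rescues the word *mediated* or the separation of the two components. Both conflict with the randomisation described in the same section, and an analysis plan would not correct them.

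**Conclusion.** The point holds in a limited form. The 2×2 layout is sound and allows the interaction to be estimated; the defects are the claim made for it and the lack of any named analysis that answers the question. The design can assess modification of the group-care effect by the combined package. It cannot assess mediation, and it cannot tell pregnancy testing from ultrasound.

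The risk of a false finding of dependence is conditional on how the by-arm results are used. It reaches 49.9% only if significance is compared between the two package strata at the plan's effect, SD, ICC and facility size. The low power of the correct contrast (about 29% at 0.5 week, 80% only near 1.0 week, twice the target effect) rests on the same upper-bound inputs, a two-sided 5% test, nine facilities per arm and no gain from matching. The primary comparison and the sample size are unaffected. The change is worth making because it is nearly free and prevents two plausible misreadings.

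**What to change.** 1. In the Study design section and the Figure 1 legend, replace the mediation wording, including the *or* between the two components, with *modified by the combined package*.
2. In the Statistical analyses section, name one exploratory group-care × package interaction contrast, (Arm 4 − Arm 2) − (Arm 3 − Arm 1), as the answer to this question. It should account for the pairs and be reported with its 95% CI.
3. State that dependence on the package will not be inferred from significance in one stratum and not the other.
4. Keep the across-arm comparisons of Table 2 for their own aims.
5. State that for gestational age at birth, under the plan's upper-bound SD and ICC and ignoring any gain from matching, the contrast has about 29% power for a 0.5-week difference in effects and 80% only near 1.0 week.

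The cost is a few words and one model term. No new data are needed and the primary analysis does not change. The small downside is that the capability claimed for the four-arm design becomes less favourable.

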**Figure 1. f1:**
[figure not shown]
Facility-level randomization of 36 health centers included in a cluster randomized controlled trial of group antenatal care and postnatal care in Rwanda. Arm 1 delivers standard antenatal and postnatal care only and is the pure control. Arm 2 delivers standard antenatal and postnatal care, with the addition of early pregnancy testing in the community and obstetric ultrasound performed by primary antenatal care providers. Arm 3 delivers group antenatal and postnatal care, and Arm 4 delivers group antenatal and postnatal care with the addition of early pregnancy testing and ultrasound. In health centers randomized to group care (Arms 3 and 4), this model will follow the opt-out standard of care for facility-based antenatal and postnatal care. This design makes it possible to analyze differences between group care and standard care and also to assess if those effects are mediated by early pregnancy testing in the community or the availability of ultrasound (especially for early gestational age assessment) at the health center. HC, health center; US, ultrasound; PT, pregnancy testing.

### Study setting

This trial will evaluate the impact of a customized group ANC/PNC model in selected health centers in the five districts with the highest rates of preterm birth recorded in the health management and information system in Rwanda and with no overlapping project in place (Bugesera, Rubavu, Nyamasheke, Nyarugenge, and Burera). Health centers are the first facility point of contact for clients and provide a minimum package of services including promotional, preventive and curative care. At health centers, nurses and midwives offer universal access to ANC and PNC. Thirty-six health centers were selected for this CRCT based on their location in one of five districts, their average monthly ANC volume, and the reported presence of more than one ANC provider at the facility on any day ANC is offered there. All of the invited health centers agreed to participate. Study sites include urban and rural settings. Outcome data is also collected from District Hospitals to which these health centers refer in the event of complications.
Figure 2 illustrates the trial design as a Consolidated Standards of Reporting Trials (CONSORT) flow diagram
^19^ following the Standard Protocol Items: Recommendations for Interventional Trials (SPIRIT) guidelines (see
*Reporting guidelines*)
^18,
20^.

**Figure 2. f2:**
[figure not shown]
CONSORT flow diagram
^19^. ANC, antenatal care; US, ultrasound; UPT, urine pregnancy test; GA, gestational age.

### Participant characteristics

Study participants include pregnant women and health care providers working in the participating health facilities. Pregnant women meeting the following criteria will be included in the primary analysis comparing the effect of group ANC versus standard ANC on gestational age at birth:

–Minimum age of 15 years at the time of enrollment–Attend ANC1 before 24 completed weeks of pregnancy–Attend more than one ANC visit at one of the 36 study facilities–Consent to participate in the study and follow up

Women who present for ANC after 24 completed weeks of pregnancy will be invited to participate in group ANC throughout the remainder of their pregnancies, and descriptive data of their attendance will be reported; however, their outcomes will not be included in the primary analysis.

Women who only attend one ANC visit at a study facility will be excluded from the primary analysis. Health care providers working in selected health facilities and providing ANC services who are willing to participate will be included in this study.

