## Abstract

**Background:** Group antenatal care has demonstrated promise as a service delivery model that may result in improved outcomes compared to standard antenatal care in socio-demographic populations at disparately high risk for poor perinatal outcomes. Intrigued by results from the United States showing lower preterm birth rates among high-risk women who participate in group antenatal care, partners working together as the Preterm Birth Initiative - Rwanda designed a trial to assess the impact of group antenatal care on gestational age at birth.

**Methods:** This study is a pair-matched cluster randomized controlled trial with four arms. Pairs randomized to group or standard care were further matched with other pairs into quadruples, within which one pair was assigned to implement basic obstetric ultrasound at the health center and early pregnancy testing at the community. At facilities randomized to group care, this will follow the opt-out model of service delivery and individual visits will always be available for those who need or prefer them. The primary outcome of interest is mean gestational age at birth among women who presented for antenatal care before 24 completed weeks of pregnancy and attended more than one antenatal care visit. Secondary outcomes of interest include attendance at antenatal and postnatal care, preterm birth rates, satisfaction of mothers and providers, and feasibility. A convenience sample of women will be recruited to participate in a longitudinal survey in which they will report such indicators as self-reported health-related behaviors and depressive symptoms. Providers will be surveyed about satisfaction and stress.

**Discussion:** This is the largest cluster randomized controlled trial of group antenatal and postnatal care ever conducted, and the first in a low- or middle-income country to examine the effect of this model on gestational age at birth.

**Trial registration:** This study is registered on ClinicalTrials.gov as
NCT03154177 May 16, 2017.

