The Preterm Birth Initiative (PTBi) – Rwanda, aims to explore both the outcomes and feasibility of a combined group ANC and group PNC model implemented in Rwanda. PTBi – Rwanda is a partnership between investigators at the University of Rwanda (UR) and University of California, San Francisco (UCSF) and national health system implementors at the Rwanda Biomedical Center (RBC) and Ministry of Health (MOH). PTBi - Rwanda’s primary aim is to reduce the burden of morbidity and mortality related to prematurity. Intrigued by results from the United States showing lower preterm birth (PTB) rates among high-risk women who participate in group ANC, these partners aim to test the hypothesis that Rwandan women receiving care at facilities that offer group ANC will have a greater GA at birth, on average, than women receiving care at facilities that offer standard ANC. In addition, partners felt an important benefit of the approach was the ability to improve adherence to recommended ANC and PNC schedules, and also considered that additional components might produce similar effects. Specifically, partners wanted to study the effects of introducing urine pregnancy testing by community health workers as part of pregnancy surveillance and the use of ultrasound at first trimester to determine GA and motivate mothers to attend ANC earlier and more often.

Rwanda’s national maternity care system provides an excellent opportunity to test this innovative service delivery model due to its well-developed community capacity, cultural foundations in community-based decision-making and cooperation, and robust existing data system such as longitudinal ANC registers. The Rwanda MOH currently recommends four focused ANC visits and four PNC visits at 24 hours, 2 days, 3-7 days, and 42 days of life. The Rwanda Demographic and Health Survey published in 2015 provided a snapshot of the contemporary utilization of perinatal services

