### Study design

The study is a pair-matched CRCT with four arms. In the five Rwandan districts selected for this study, we assessed 55 health centers to inform study design and site selection. First, we limited the data set to only those with an average of at least 48 first ANC per month, operating on the assumption that this would allow for formation of at least 2-4 ANC groups in the event the health center was allocated to the intervention. This gave us 50 potential health centers. We then limited to those that had more than one ANC provider during ANC days, which reduced the available health centers to 37. In total, 36 health centers (one was not matched to ensure pairing) were selected to participate in the study (see
*Extended data*: File 15)
^18^.

Next data on all other criteria for each health center was used to perform nonbipartite pair matching in R producing a list of strongest potential matches across all criteria. The study team then reviewed the possible matches and agreed on optimal pairings among facilities that had at least 2 ANC providers prioritizing matches with similar volume of ANC1 visits, and similar distance to the nearest district hospital. Within each pair, one facility was randomized to group ANC and PNC using a computer-generated random assignment and the other was randomized to continue delivering the standard models of focused ANC and PNC. Selected health centers were pair-matched based on 1) number of ANC providers, 2) ANC volume 3) delivery volume, 4) proportion of ANC1 before 16 weeks gestation, 5) baseline PTB rate, and 6) availability of key screening tests. Pairs were then further matched into quadruples by the study team based on ANC volume, where one pair within each quadruple was randomly assigned using a computer-generated random assignment to additionally implement basic obstetric ultrasound at the health center and early pregnancy testing at the community level and the other was not. No allocation concealment was used.

Therefore, each study facility has one of the four assignments as illustrated in

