*Extended data*: File 10). Process measures of interest are the time spent on each ultrasound examination and the timing of the ultrasound (whether it was completed as part of a routine ANC visit or as a separate visit). At the community level, a UPT monthly form will be used to report on number of women tested, test results and referrals granted (
*see Extended data*: File 11)
^18^. These data will also be captured by the data collector in Research Electronic Data Capture version 2.35 (REDCap)
^23^.

Data elements are collected at enrollment (ANC 1 visit), during later ANC visits, delivery, and at PNC visits in the health center. In cases where a mother had a complication and was referred to the district hospital, usually the closest district hospital located within the catchment area, data collectors will find these data in the hospital registers. Data collectors are also responsible for monitoring the cohorts on a routine basis. This tracking process should alert staff when mothers do not attend ANC visits, give birth at a different facility, or do not attend PNC. Those who have not attended PNC by 12 weeks after the expected delivery date will be followed up by facility record review, telephone, or in immunization clinics to minimize loss to follow up.
Table 3 displays the data collection strategy for each measure that will be analyzed and reported. Data collectors will also report adverse events and protocol violations (see
*Extended data*: Files 1 and 2)
^18^.

**Table 3. T3:** Outcome main indicators and data sources.

Outcome	Outcome indicator	Analysis Group	Source
**Gestational age**	GA (Recorded GA at birth VS. LMP- calculated GA)	All live births (Apgar > 0 at 1 min)	MAT Register
**28-day infant mortality among** **preterm neonates**	Preterm neonates dead at 28 days Preterm neonates alive at 28 days Preterm neonates lost to follow-up at 28 days	All live births (Apgar > 0 at 1 min) with GA < 37 weeks	MAT & NEO Register, RapidSMS
**42-day infant mortality among** **preterm neonates**	Preterm neonates alive at 42 days Preterm neonates dead at 42 days Preterm neonates lost to follow-up at 42 days	All live births (Apgar > 0 at 1 min) with GA < 37 weeks	PNC & Immunization Register, RapidSMS
**Adherence: four ANC visits**	Women who attended four ANC	All women who attended ANC 1	ANC Register
**Adherence: six-week PNC**	Women who attended PNC 1	All women who attended ANC 1	PNC Register

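### Excluding women with only one ANC visit makes the primary analysis depend on behaviour after randomisation, so it is not intention-to-treat and is at risk of selection bias

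*Protocol article*

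**What the plan says.** The restriction appears three times in the protocol article. Under Participant characteristics it is an inclusion criterion for the primary analysis ("Attend more than one ANC visit at one of the 36 study facilities") and then an explicit exclusion ("Women who only attend one ANC visit at a study facility will be excluded from the primary analysis"). In the Abstract it is part of the primary outcome, which is mean GA at birth among "women who presented for antenatal care before 24 completed weeks of pregnancy and attended more than one antenatal care visit".

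Other sections fix the order of events and the role of attendance:

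- **Study design:** within each matched pair, "one facility was randomized to group ANC and PNC using a computer-generated random assignment".
- **Study interventions:** the first visit is a standard individual visit in every arm, and the invitation to group care comes at its end. Table 1 makes the second visit the first group visit.
- **Introduction:** an important expected benefit of the approach is its "ability to improve adherence to recommended ANC and PNC schedules". Table 2 lists ANC attendance as a secondary outcome.
- **Statistical analyses:** the primary model is described as "Unadjusted, intention-to-treat generalized estimating equations (GEE) linear regression". The Discussion also describes the approach as intent-to-treat.
- **Data collection:** all enrolled women are to be followed through birth to 42 days. Table 3 gives the GA analysis group as "All live births (Apgar > 0 at 1 min"), with no condition on number of visits.

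The article gives no reason for the exclusion and describes no analysis that keeps one-visit women.

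**The concern.** Randomisation makes the two sets of facilities comparable in the women who arrive. It does not make them comparable in the women who come back, if coming back depends on what was offered. Here the trial itself expects the offer to affect return. If group care brings back women who would have stopped after one visit under standard care, those women are analysed in the group arms while their counterparts in the standard arms are dropped. Any difference between them and the other women in expected GA then appears as a treatment effect.

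The filter is also partly tied to the outcome, because a woman whose pregnancy ends before a second visit is excluded for that reason. Referral may add to this. Box 1 leaves it to the hospital doctor whether a referred woman continues at the health facility, so some higher-risk women may have only one study-facility visit.

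At stake is the interpretation of the primary result. A larger sample does not remove this kind of bias, and the analysed data alone would not show its direction.

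**Working it through.** **1. The plan's own figure.** Inputs from Sample size: SD 4.3 weeks, ICC 0.01, 36 facilities (18 per side in the main comparison of Arms 1+2 with Arms 3+4), 214 observations per facility, difference 0.5 weeks, 5% significance (taken as two-sided), 80% power.

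- Design effect: 1 + 213 × 0.01 = 3.13.
- SE = √(2 × 4.3² × 3.13 / (18 × 214)) = √(115.75 / 3852) = 0.173 weeks.
- Power for 0.5 weeks, noncentral t with 34 df: 80.0%. The smallest cluster size reaching 80% is 214, so the stated figure reproduces.
- 214 / 0.70 = 305.7, rounded up to the stated 306.

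**2. Bias under no true effect.** Let pC and pT be the shares with only one visit under standard and group care. Assume group care brings some women back and drives none away.

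- Women who would have one visit in either arm are excluded from both and cancel.
- Women who would return in either arm are included in both.
- The analysed sets differ only by the women retained because of group care. They form (pC − pT)/(1 − pT) of the analysed group-care women.
- If their mean GA differs by D from that of the women who return in either arm:

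bias (group − standard) = (pC − pT)/(1 − pT) × D.

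The document gives none of pC, pT or D. The following inputs are assumptions:

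| pC | pT | D (weeks) | Bias (weeks) |
|---|---|---|---|
| 5% | 2% | −2 | 0.03/0.98 × (−2) = −0.06 |
| 10% | 5% | −2 | 0.05/0.95 × (−2) = −0.11 |
| 15% | 5% | −2 | 0.10/0.95 × (−2) = −0.21 |
| 20% | 10% | −3 | 0.10/0.90 × (−3) = −0.33 |

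The negative sign comes from assuming that the retained women deliver earlier. A positive D reverses it. If the same share and type of woman return in both arms, the bias is zero.

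**3. Consequence at the design SE (0.173 weeks, t with 34 df).**

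| Absolute bias (weeks) | Two-sided type I error | Power for a true 0.5 weeks if the bias runs against group care |
|---|---|---|
| 0 | 5% | 80% |
| 0.10 | about 9% | about 61% |
| 0.20 | about 20% | about 39% |

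**4. Numbers alone are not the problem.** If exclusion simply removed 10% or 20% of the 214, power would be 78.6% or 77.0%.

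**5. Dilution if one-visit women are included.** Suppose 10% have one visit and get no benefit. The expected difference is 0.90 × 0.50 = 0.45 weeks. At the same SE, power falls from 80% to about 71%.

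**The case against.** - **The bias is not demonstrated.** A reader might infer that the comparison is biased and the benefit of randomisation lost. The document does not support that. Bias needs the share or type of one-visit women to differ by arm in a way related to GA, and no figure is given for either. This objection stands: the supported statement is a risk of unknown size and sign.
- **Timing of the second visit.** A reader might infer from Table 1 that the second visit falls at a different gestation in group care, so that early births are filtered differently. The article gives no visit timings for standard care. Individual visits stay available at group-care sites, and the rule does not require the second visit to be a group visit. No difference in timing by arm can be derived.
- **A simpler size estimate overstates.** It is tempting to multiply the difference in one-visit shares by the average GA gap of all one-visit women. Suppose 5% never return in either arm and deliver 5 weeks early, and a further 10% fail to return only under standard care and deliver 0.5 weeks early. The average gap is (0.05 × 5 + 0.10 × 0.5)/0.15 = 2.0 weeks, so the shortcut gives 0.10 × 2.0 = 0.20 weeks. The bias is 0.10 × 0.5/0.95 = 0.05 weeks. This is why the formula above counts only women retained because of group care.
- **The change comes late and repairs only part.** Study status says that data collection ended on December 31, 2018 and that analysis is under way. Allocation was not concealed, and only 70% follow-up is assumed, so births of one-visit women may be selectively missing. These points affect how the change is made and reported. They do not justify the restricted set as the only analysis under an intention-to-treat label.
- **Live births only.** Table 3's live-birth denominator can be read together with the eligibility list. How stillbirths are handled is a separate, minor matter.

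**Conclusion.** The concern holds as a risk of bias and as a wrong label. The primary population is defined by an event that follows both randomisation and the group-care offer, that the trial expects group care to influence, and that an early end of pregnancy prevents. An analysis restricted in this way is closer to per-protocol than to intention-to-treat.

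Neither size nor direction can be derived from the document. The range of about 0.06 to 0.33 weeks is illustrative. It rests on assumed one-visit shares and GA gaps, and on group care driving no woman away. The type I error figures rest on the plan's own SD, ICC and cluster size. Even the lower half of that range is not negligible beside a 0.5-week target.

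The criterion of a first visit before 24 weeks is settled before the group-care offer and does not raise the same problem.

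**What to change.** - Define the intention-to-treat analysis as all consenting women aged 15 or over whose first ANC visit was before 24 completed weeks, analysed by facility allocation whatever their later attendance. Document the change as made after data collection and before the arm comparison is seen.
- Keep the more-than-one-visit set as a supportive analysis, labelled as not intention-to-treat.
- If the pre-stated population must stay primary, remove the intention-to-treat label from it and report the all-women analysis beside it with equal prominence.
- Report, by arm, the share of women with one visit and the completeness of birth outcomes.
- Make the Abstract, Participant characteristics, Statistical analyses and Table 3 agree on who is analysed for GA.

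**Cost.** No new enrolment is needed, because all enrolled women were to be followed through birth and tracking covers missed visits and births elsewhere. There are three downsides. Dilution lowers power (about 71% in the 10% example). Births of one-visit women are harder to trace, so some selection through missing outcomes may remain. Changing the primary population after data collection needs a transparent record.
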